### Outcomes {12}

The study’s primary outcomes are as follows: (a) RISEinFAMILY implementation: proportion of families completing basic and advanced training levels (observed vs expected), average time to complete basic and advanced training levels (observed vs expected) and average time of kangaroo care per day (hours); (b) short-term health infant’s outcomes: proportion of high-risk infants achieving and maintaining adequate growth patterns during NICU admission, defined according to Patel’s method [10, 11].

The study’s secondary outcomes are as follows: reported adverse event rate per 1000 patients/day, feeding patterns and major morbidities at 36 weeks postmenstrual age (PMA) or discharge, nosocomial infection [12], necrotising enterocolitis (Bell’s > stage 2), moderate-severe brain injury (worst cranial ultrasound) [13], parental needs, empowerment and psychological health (stress [14], anxiety and depression [15, 16], self-efficacy [17], bonding [18], resilience [19]), professional’s self-care and satisfaction (anxiety and depression [15], burnout [20], post-traumatic stress [21], work and well-being [20]).

The study’s exploratory outcomes are as follows: economic impact (level of post-implementation utilisation of FICare, resources and costs associated with FICare implementation, cost-effectiveness estimates compared to the current care, expected value of current implementation and expected value of perfect implementation); mid-term infant’s general health (growth pattern during the first 12 months from birth, use of health system facilities after discharge); long-term neurodevelopment (survival without neurodevelopmental disabilities).

Specific items and test batteries are stated in Additional file 1.

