### Sample size {14}

No previous study has assessed the effect of FICare intervention on growth velocity expressed in g/kg per day. Therefore, for sample size calculation in the RISEinFAMILY project, we will follow one of the most recent studies evaluating the effect of individualised breast milk fortification on weight gain expressed in the same units [34]. In this study, based on their own data obtained in a pilot and other literature data, the authors assumed 1.8 ± 3.1 g/kg/d as a reasonable and clinically meaningful difference in weight gain. With a total *N* of 103 (experimental group *N* = 52, control group *N* = 51), they found a difference in the weight gain of 1.9 g/kg/d and a standard deviation of 2.5 g/kg/d.

Using this information, we calculated the minimum size for the intervention (FICare) and the control (standard care) group in the RISEinFAMILY study. Our null hypothesis is no impact of FICare and, as a consequence, the mean of the weight gain in both the intervention and control groups will be the same. Our alternative hypothesis is a difference in the mean weight gain between FICare and the control group of at least 1.9 g/kg/d [34]. We impose a type I error (probability of rejecting the null hypothesis when it is true) of 5% (*α* = 0.05), and a type II error (probability of not rejecting the null hypothesis when it is false) also of 5% (> 0.05), which provides a statistical power of 95%. The minimum sample size for intervention and control groups is given by at least 46 children in the intervention (FICare) and other 46 children in the control (standard care) group.

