For our primary hypothesis, we will compare infant standardised weight gain velocity between the two groups over the 4-week study period using generalised linear mixed modelling (GLMM). For our primary outcome, we will compare infant standardised weight gain between the two groups over the study period defined as the change in Patel’s growth pattern measured weekly from enrolment until day 28 post-enrolment, testing an interaction term between group and post-baseline weight measurements. We will adjust for additional covariates using a hybrid approach, forcing in known confounders of gestational age and study site and using backward stepwise selection to retain covariates that contributed *p* < 0.1 to the final model from potential confounders. Additionally, we will conduct sensitivity analyses by adding in weight measured at discharge.

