### Methods for additional analyses (e.g. subgroup analyses) {20b}

Important prognostic variables are centre, sex and gestational age, or main neonatal diagnosis. These will be used as additional independent variables in key secondary logistic regression models for secondary subgroup analysis.

Further subgroup analysis will be conducted in line with the primary analysis, where the endpoint is dichotomous. For continuous endpoints, similar modelling strategies will be used, but instead of logistic regression linear regression models will be used.

The cost-effectiveness analysis of RISEinFAMILY implementation will be carried out using recommended methods [35, 36]. A decision-analytical [37] will be developed and populated with costs and effectiveness data from the pilot studies. For each RISEinFAMILY implementation site, the cost-effectiveness of the intervention will be estimated. The cost-effectiveness and the value of implementation analyses will be conducted for the seven neonatal units involved in the study. The mean net monetary benefit per participant will be calculated using the health care system willingness-to-pay threshold corresponding to the current cost of neonatal care in the NICU.

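### The primary growth outcome is a proportion in the Outcomes section but a mean weight gain in the sample size and analysis, and the stated interaction term does not clearly test either.

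*Protocol article*

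**What the plan says.** All places are in the protocol article.

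- **Outcomes {12}.** The infant primary outcome is the "proportion of high-risk infants achieving and maintaining adequate growth patterns during NICU admission". This is binary per infant, refers to high-risk infants and covers the NICU stay.
- **Sample size {14}.** Under the null hypothesis "the mean of the weight gain in both the intervention and control groups will be the same"; the alternative is "a difference in the mean weight gain between FICare and the control group of at least 1.9 g/kg/d". The SD comes from a cited trial of breast milk fortification, where "they found a difference in the weight gain of 1.9 g/kg/d and a standard deviation of 2.5 g/kg/d". With 5% type I and 5% type II error, the result is at least 46 infants per group.
- **Statistical methods {20a}.** The primary hypothesis concerns standardised weight-gain velocity over a 4-week period, by generalised linear mixed model. The next sentence describes the primary outcome as a change in growth pattern, "measured weekly from enrolment until day 28 post-enrolment, testing an interaction term between group and post-baseline weight measurements". Discharge weight enters only as a sensitivity analysis.
- **Trial design {8}.** At least 552 infants are planned.
- **Eligibility criteria {10}.** For infants admitted for other peri-neonatal conditions, an anticipated stay of at least 7 days is enough.

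**The concern.** A confirmatory analysis needs one variable, one population, one window and one model term that estimates the effect in the hypothesis. Here the outcome definition points to a difference in proportions over the NICU stay, while the hypothesis and sizing point to a difference in means. The only model term that is spelled out is an interaction with post-baseline weights, and those weights are what weight gain is computed from.

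Two things are at stake. First, a result on the proportion, on mean velocity or on the interaction could each be reported as the primary result. Allocation is not randomised and hospitals and staff are not blinded, so a clear prior choice is an important safeguard. Second, if the interaction is fitted as written, its p-value does not answer the question in the null hypothesis.

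**Working it through.** **1. Reproduce the plan's figure.** Inputs from Sample size {14}: difference 1.9, SD 2.5, type I error 0.05, power 0.95. Sidedness is not stated; two-sided is taken.

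- Normal approximation: n = 2 × [2.5 × (1.960 + 1.645) / 1.9]² = 44.996, so 45 per group.
- Two-sample t-test: n = 45.98, so 46 per group, with power 95.0% at 46.
- A one-sided test (normal approximation) would give 38.

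The 46 is correct for a two-sided, individual-level comparison of two means.

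**2. Set the sections side by side.**

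| | Outcomes | Sample size | Statistical methods |
|---|---|---|---|
| Variable | proportion with adequate growth | mean weight gain, g/kg/d | weight-gain velocity; weekly change in growth pattern |
| Infants | high-risk | no such restriction | no such restriction |
| Window | NICU admission | not stated | enrolment to day 28 |

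The sample size and the first sentence on the primary hypothesis broadly share one continuous variable. The clear break is between these and the Outcomes section. The windows need not coincide, because some infants may leave before day 28 and others stay longer. The document gives no length-of-stay figure, so the number affected is unknown.

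**3. Does the 46 carry over to the proportion?** The document gives neither a control proportion nor a target difference. As an illustration, assume normal velocities and turn the same shift, 1.9/2.5 = 0.76 SD, into a proportion: p1 = Φ(Φ⁻¹(p0) + 0.76). Use the pooled two-proportion formula, two-sided 0.05, no clustering.

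| Assumed control p0 | p1 | Power at 46 per group | n per group for 95% |
|---|---|---|---|
| 0.3 | 0.593 | 82% | 72 |
| 0.4 | 0.694 | 82% | 72 |
| 0.5 | 0.776 | 80% | 76 |
| 0.6 | 0.845 | 75% | 85 |
| 0.7 | 0.900 | 68% | 101 |

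So the 95% attached to 46 per group is not the power for the proportion.

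**4. Does this show an underpowered trial?** No. Note that 5 × 92 + 2 × 46 = 552, which suggests 46 per group per site, although the document does not say so. On that reading sites 1–5 supply 5 × 46 = 230 per group, and the formula above gives over 99.9% power for p0 of 0.3 to 0.7. If only half of the 552 infants entered the comparison (138 per group), it would give 98.9% or more. Both ignore clustering.

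**5. What does the interaction estimate?**

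- *Literal reading.* With velocity V as response and post-baseline weight W as predictor, V = a + b·group + c·W + d·group·W. The coefficient d is the between-group difference in how V relates to W. If every intervention infant gained 1.9 g/kg/d more and that relation were the same in both groups, d would be 0. W also enters the calculation of V, so part of the response is on both sides.
- *Group-by-week, velocity as response.* A constant difference of 1.9 in each week gives an interaction of 0. The term asks whether the difference changes, not whether it exists.
- *Group-by-week, log weight as response.* Under roughly exponential growth, 1.9 g/kg/d is 0.0019 per day, or 7 × 0.0019 = 0.0133 per week on the log scale. Here the interaction is the difference in growth rate and does test the hypothesis.

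Only the last reading, or its analogue on weight, fits the hypothesis. The text names velocity and change in growth pattern, and does not name weight as the response.

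**The case against.** Four points can be made for the plan.

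- **Power.** A reader might infer from the table of proportions that the trial is underpowered. The documents do not support this: 46 per group is a minimum, 552 infants are planned, and the control proportions are assumed. What stands is that the stated justification belongs to a different endpoint.
- **The test.** A reader might infer that the term is invalid under any reading. It is not. The sentence speaks of weekly measurements, so group by measurement occasion may be meant, and with weight as the response that is a sound test of growth rate. What stands is that the wording does not say so and, read literally, specifies something else.
- **The subgroup section.** The sentence "Further subgroup analysis will be conducted in line with the primary analysis, where the endpoint is dichotomous" might be taken as a further contradiction that declares the primary analysis binary. It can equally be conditional, because the next sentence deals with continuous endpoints. It is not counted here and needs no correction on this ground.
- **The window.** Weekly data entry runs to discharge, there is a rule for step-down units, and a sensitivity analysis adds discharge weight. This softens the conflict. A sensitivity analysis does not, however, turn a day-28 analysis into the outcome defined over the NICU stay.

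An unseen analysis plan could choose one version, but it would then contradict at least one section of this protocol.

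**Conclusion.** The point holds as a mismatch that is certain from the current text. The Outcomes section names a proportion in high-risk infants over the NICU stay; the sample size and analysis concern mean weight gain, with the analysis running to day 28. The sizing is right for a comparison of means and gives no support to the proportion. At the 46-per-group minimum, and only under the assumptions of step 3, power for the proportion would be 68–82% instead of 95%; this is an illustration, not an estimate for the planned trial.

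The interaction as worded does not estimate the mean difference in the null hypothesis. It becomes a valid test of growth rate only under an unstated choice of response and time term. The primary analysis should not be run until both matters are settled in the protocol.

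**What to change.** Name one primary growth measure, one infant population and one time window, and use them in Outcomes, Sample size and Statistical methods.

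- The choice that fits the existing hypothesis and sizing is mean weight-gain velocity in g/kg/d from enrolment to day 28, or to discharge if earlier, in a stated infant population. The adequate-growth proportion then becomes a key secondary outcome.
- If the investigators prefer to keep the proportion as primary, restate the sample-size justification for it, with an assumed control proportion and target difference, and align the analysis.
- For the velocity option, replace the interaction by the main group effect on velocity, or by group-by-week with weight or log weight as the named response.

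The cost is a protocol and registry amendment. No new measurement is needed: the activity scheme lists weight at enrolment, during the intervention and at its end, and data entry is weekly up to discharge. Enrolment has begun, so the change should be made and dated before outcome data are compared between groups.

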### Interventions

#### Explanation for the choice of comparators {6b}

A cohort of patients, born at clinical sites 1 to 5 from the beginning of the study to the time assigned to start the intervention, will be assigned to the control group, representing standard neonatal care.

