#### Intervention description {11a}

The study will start at the same time at all participating sites that will continue to provide routine clinical care according to their current policies. Prospective data gathering will be accomplished.

A start point for the experimental intervention (3, 6, 9, or 12 months from the start of the study) will be assigned for each clinical site (1 to 5) taking into account the expected time internally needed to overcome all logistics and regulatory issues with a potential impact on FICare implementation. A 3-month wash-out period will be used for the local training process and assessment of site readiness, while enrolment will be halted. After that, recruiting will continue, and the experimental intervention will be started. Clinical sites 6 and 7 will run the experimental intervention from the start of the study, without pauses.

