## Assignment of interventions: allocation

### Sequence generation {16a}

In this non-randomized study, the allocation sequence is not generated using computer-generated random numbers. Instead, the allocation is based on considerations aimed at achieving an equitable distribution of patients between the control and intervention groups.

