## Discussion

This international multicenter trial focusing on FICare marks a significant milestone in the field as it explores the scalability of FICare across diverse geographical and sociocultural contexts. This comprehensive research study protocol aims to fill gaps in existing literature and advance knowledge in the field by outlining the study design, methodology, and objectives. The trial employs a stepped wedge cluster controlled trial design to provide strong evidence on the impact of FICare. This type of study design not only offers practical and ethical benefits but also enhances generalisability by accounting for confounding effects from factors such as hospital culture, policies, architecture, and size. The analysis also considers the interaction of time, acknowledging the potential growth of parental involvement in neonatal care practices.

Key outcomes of interest include short-term newborn health, parental mental health, and healthcare professional satisfaction. The collaborative co-design process strengthens the study by involving various stakeholders and ensuring the relevance and applicability of the findings. Additionally, the study examines economic outcomes in different developmental countries to provide insights into the cost-effectiveness of implementing FICare.

While a limitation of this study is the lack of blinding for participants and researchers, it is anticipated to have minimal impact at the individual patient level, as researchers cannot manipulate medical facts or influence parental responses. Although there is a potential bias from non-blinding healthcare professionals who may have pre-existing support for FICare, this bias is expected to be insignificant. Objective outcomes at the cluster level, such as cost-effectiveness, are not anticipated to be affected by bias.

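### The stated primary growth model has no calendar-time term, so a secular trend is confounded with the intervention within each of sites 1-5: fully if time is omitted, partly if it is left to p < 0.1 selection

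*Protocol article*

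**What the plan says.** The protocol article, section {20a}, sets out the primary growth model. It is a generalised linear mixed model comparing the two groups over four weeks from enrolment, "forcing in known confounders of gestational age and study site and using backward stepwise selection to retain covariates that contributed" p < 0.1. The one interaction it names is described as "testing an interaction term between group and post-baseline weight measurements". Those measurements are weekly from enrolment to day 28, so this is the infant's follow-up time and not calendar time. The simpler between-group tests in the same section carry no time adjustment either.

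The design sections fix the order of exposure. Under {6b}, controls are the infants "born at clinical sites 1 to 5 from the beginning of the study to the time assigned to start the intervention". Under {11a} the plan assigns each of sites 1-5 "A start point for the experimental intervention (3, 6, 9, or 12 months from the start of the study", followed by a pause: "A 3-month wash-out period will be used for the local training process and assessment of site readiness, while enrolment will be halted". Under {16a}, "the allocation sequence is not generated using computer-generated random numbers". Also under {11a}, "Clinical sites 6 and 7 will run the experimental intervention from the start of the study, without pauses".

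The Discussion adds: "The analysis also considers the interaction of time, acknowledging the potential growth of parental involvement in neonatal care practices". It gives no term, time scale or model.

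**The concern.** In a stepped wedge, each switching site contributes its control infants early and its intervention infants late. Adjusting for site removes differences between sites, but what remains is a before-after contrast within each site. Only a calendar-time term lets the sites that have not yet switched, or have always been exposed, show what would have happened anyway.

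The adjustment set is stated here and not deferred: two variables are forced in and the rest go to selection. Under that statement, a gradual change in weight gain over the 32 months would be credited, wholly or in part, to RISEinFAMILY. The Discussion itself raises possible growth in parental involvement, which is the behaviour that the intervention targets. Because start times follow local logistics, randomisation of the order gives no protection either.

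**Working it through.** **Inputs from the protocol article.** Start points 3, 6, 9 or 12 months for sites 1-5 and a 3-month pause ({11a}); at least 552 infants over 32 months ({8}); target difference 1.9 g/kg/d, SD 2.5, alpha 0.05, power 95%, 46 per group ({14}).

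**Assumptions, because the article does not give them.** Size of the trend (0.25 and 0.5 g/kg/d per year, linear), accrual pattern, the start shared by two of the five sites, and the intracluster correlation (set to zero). I take 92 infants at each of sites 1-5 and 46 at each of sites 6-7. This is an inference that fits the total: 5 × 92 + 2 × 46 = 552.

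**The plan's own figure.** n = 2 × (1.960 + 1.645)² × 2.5² / 1.9² = 45.0 per group. The two-sample t version gives 45.98, so 46, and the stated size reproduces. That calculation has no site, period or cluster term.

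**Gap in calendar time between a site's control and intervention infants**, for a site starting at month s:

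- Intervention enrolment runs to month 32: control midpoint s/2, intervention midpoint (s + 3 + 32)/2, difference 35/2 = 17.5 months for every s.
- Intervention phase only as long as the control phase: intervention runs from s + 3 to 2s + 3, midpoint 1.5s + 3, difference s + 3. With starts 3, 6, 6, 9, 12 the mean is 7.2 + 3 = 10.2 months; with 3, 6, 9, 12, 12 it is 8.4 + 3 = 11.4.

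**Bias and false positives with time omitted.** Bias = monthly trend × gap. False-positive rate = Φ(bias/SE − 1.96) + Φ(−bias/SE − 1.96). With 46 + 46 per site, SE = 2.5 × √(2/230) = 0.233. With even accrual to month 32, a site has 92 × s/29 controls. For starts 3, 6, 6, 9, 12 the sum of n_c × n_t / 92 over sites is 8.5 + 15.1 + 15.1 + 19.7 + 22.3 = 80.7, and SE = 2.5/√80.7 = 0.278.

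| Layout | Gap (months) | SE | Trend 0.25/year: bias, false positives | Trend 0.5/year: bias, false positives |
|---|---|---|---|---|
| 46 + 46, equal phases, starts 3, 6, 6, 9, 12 | 10.2 | 0.233 | 0.21, 15% | 0.42, 45% |
| 46 + 46, equal phases, starts 3, 6, 9, 12, 12 | 11.4 | 0.233 | 0.24, 17% | 0.47, 53% |
| Even accrual to month 32 | 17.5 | 0.278 | 0.36, 26% | 0.73, 75% |
| 46 + 46, intervention to month 32 | 17.5 | 0.233 | 0.36, 35% | 0.73, 88% |

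Against the 1.9 target, the biases are 11-19% (trend 0.25) and 22-38% (trend 0.5).

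**Linear calendar time left to backward selection at p < 0.1** (2,000 simulations per scenario, sites 1-5, 46 + 46, starts 3, 6, 9, 12, 12):

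- No trend: false-positive rate 8-9%.
- Trend 0.5 per year: time is retained in only 30-50% of trials, the residual bias is about 0.20, and the false-positive rate is 41-46%.
- Trend 1.0 per year: time is retained in 73-95% of trials, and most of the bias goes.

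**Calendar quarter forced in** (same simulations): the false-positive rate is 4-6% for every trend from 0 to 1.0 per year.

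**Price in precision.** Power = Φ(1.9/SE − 1.96). On sites 1-5 the SE rises to about 0.6-0.8 across the layouts with the fifth site starting at month 6 or 12. At 0.595 power is 89%; at 0.80 it is Φ(0.415), about 66%. With sites 6-7 added the SE is about 0.43-0.52 and power about 99% down to 96%. None of this allows for intracluster correlation.

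**The case against.** The best defence is that a condensed article need not list every model term. Section {20a} speaks of additional covariates, so a core model with a time effect may exist in the full protocol, and the Discussion says that time is considered. It is therefore right not to claim that the final analysis is known to omit time. But the article does say what is forced in and how everything else is chosen. A Discussion sentence with no term or scale does not change that, and the two places do not agree as written.

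A reader might also infer that any secular trend would pass in full into the effect estimate. That holds only if calendar time is absent. If it is a candidate for selection, a strong trend is usually retained and the bias is partial; moderate trends are where selection fails.

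Nor should one read the 17.5-month gap as a fact of the design. It needs enrolment up to month 32, and with even accrual only about 114 of 460 infants at sites 1-5 would be controls (starts 3, 6, 6, 9, 12). That sits badly with the balanced distribution sought in {16a} and {17a}, which is why a range is shown. Finally, the Discussion mentions possible growth in parental involvement. It does not predict a trend in nutrition or in weight gain.

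The cost of the remedy is a fair objection too. The last site restarts by month 15 (12 + 3), so later periods hold no control infants, and a period-adjusted estimate from sites 1-5 alone loses much precision.

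**Conclusion.** The point stands. As stated, the primary growth model is a within-site before-after comparison at five sites with non-randomised start times, and nothing in it separates RISEinFAMILY from calendar time. The direction of the problem follows from the design; its size depends on a trend that the documents do not give.

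Under the assumptions above and with time omitted, the whole range is a gap of about 10-17.5 months, a bias of about 0.21-0.36 g/kg/d and 15-35% false positives for a trend of 0.25 per year, and about 0.42-0.73 and 45-88% for a trend of 0.5. Leaving time to p < 0.1 selection reduces the bias but does not restore the 5% error rate. The Discussion's statement on time does not repair the model and has to be reconciled with it.

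**What to change.** In {20a}, name calendar period (for example step or quarter) as a fixed effect in the primary model beside study site, and exempt it from backward selection. Include sites 6-7 in that model to help estimate the period effects, or state why not. Their use assumes that calendar changes at the always-exposed sites resemble those at sites 1-5, and the text should say so. Rewrite the Discussion sentence so that it describes this term. Restate power for the period-adjusted model in {14}, with an assumed intracluster correlation.

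The change needs wording and a new power calculation but no new data, and it should be made before the database is closed. The cost is precision: the SE goes from about 0.23-0.28 to about 0.6-0.8 on sites 1-5 (power for 1.9 g/kg/d about 66-89%, against the planned 95%), or to about 0.43-0.52 with sites 6-7 (about 96-99%), before any intracluster correlation. A random site-by-period term, a small-sample correction for few clusters, and a fixed covariate list in place of selection are worth discussing, but they are secondary modelling choices and this point does not depend on them.

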## Statistical methods

### Statistical methods for primary and secondary outcomes {20a}

The primary analysis will be conducted in the intention-to-treat (ITT) population including all enrolled patient-family dyads who received at least one task training according to protocol procedures.

Descriptive statistics will be recorded for each group with mean, median and standard deviation for numerical variables and absolute and relative frequencies for categorical variables. 95% confidence intervals (CIs) will be provided. Comparisons between control and intervention groups will be performed using chi-square tests for categorical variables, analysis of variance for normally distributed continuous variables, and Mann–Whitney or Kruskal–Wallis tests for non-normally distributed continuous variables. Through a mixed-methods research approach and techniques both quantitative and qualitative, the following impacts will be evaluated: (a) effect of intervention: the control and the intervention group dataset from the non-FICare-experienced centres will be compared; (b) effect of “expertise” on outcomes: comparisons will be conducted between datasets from already trained FICare centres and those from the non-FICare-experienced centres.

Socio-economic sustainability: Health economics analysis based on the value of implementation framework will be conducted to assess the cost-effectiveness of RISEinFAMILY implementation strategies. The difference between the total net benefit of perfect adoption and the total net benefit of current implementation will generate the expected value of perfect implementation (positive values would characterise cost-effective implementation strategies). The analysis will also allow identifying differences in delivering RISEinFAMILY in different countries/health care settings.

Psychological assessment of experiences collected by either the NICUs staff and the families enrolled in the pilots will be conducted. Gender differences will be explored in relation to socioeconomic and cultural background.

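### The primary growth model forces in gestational age and site but not calendar time, so any drift in weight gain across the stepped roll-out is read as an intervention effect

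*Protocol article*

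**What the plan says.** Section {20a} of the protocol article describes a generalised linear mixed model for standardised weight gain to day 28 after enrolment. Covariate adjustment is hybrid: "forcing in known confounders of gestational age and study site", then "using backward stepwise selection to retain covariates that contributed" p < 0.1 from a pool of potential confounders that is not listed. The one interaction is described as "testing an interaction term between group and post-baseline weight measurements". The effect of the intervention is to be judged within sites 1-5: "the control and the intervention group dataset from the non-FICare-experienced centres will be compared".

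The timing comes from section {11a}: "A start point for the experimental intervention (3, 6, 9, or 12 months from the start of the study", assigned to sites 1-5, with a 3-month halt in enrolment before intervention recruitment begins. Sites 6 and 7 deliver the intervention throughout. Section {6b} defines controls at sites 1-5 as infants born before their site's start point, and section {16a} says the sequence is not randomised.

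The Discussion states: "The analysis also considers the interaction of time, acknowledging the potential growth of parental involvement in neonatal care practices".

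**The concern.** At each of sites 1-5 the controls are the earlier infants and the intervention infants the later ones. Group is therefore confounded with calendar time by design. A stepped wedge deals with this through staggered starts: at a given date some sites have crossed over and others have not, and a model with period effects uses that contrast. A model with site but no period ignores it and reduces to five before-after comparisons pooled together.

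The interaction that is named concerns weekly weights after each infant's enrolment. That is time within the infant's stay, not calendar time. Sites 6 and 7 do not help either. They have no control phase, so once site is in the model they contribute to the group contrast only by informing a time trend, and the model contains none.

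Any change over the recruitment period in feeding practice, staffing, case mix or weighing would enter the growth effect. It could create an apparent benefit or hide a real one.

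**Working it through.** **Inputs from the protocol article.** Recruitment of 32 months and at least 552 infants ({8}); starts at 3, 6, 9 or 12 months for five sites, so at least one start is shared, and a 3-month halt ({11a}); target difference 1.9 g/kg/d, SD 2.5, alpha 5%, power 95%, 46 per group ({14}).

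**Assumptions.** Even accrual per open site-month; intervention recruitment to month 32; one start time shared by two sites; independent infants, with no cluster correlation; a linear drift common to all sites. The documents give no drift rate, so a range is shown.

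**The plan's own figure.** n per group = 2 × (1.960 + 1.645)² × (2.5/1.9)² = 2 × 12.995 × 1.731 = 45 by normal approximation; the t-based calculation gives 46 (power 0.950). The stated 46 reproduces with two-sided alpha. It is a two-group calculation with no time or cluster term.

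**Distance between phases.** For a site starting at month s, the control mid-point is s/2 and the intervention mid-point is (s + 3 + 32)/2. The difference is 35/2 = 17.5 months, whatever s is. Bias of the site-only model = drift per year × 17.5/12 = 1.458 × drift.

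**Infants.** Sites 1-5 have 5 × 29 = 145 open site-months; sites 6-7 have 2 × 32 = 64; the total is 209. Accrual is 552/209 = 2.64 per site-month, about 383 infants at sites 1-5.

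**Standard error, site only.** The information from each site is s(29 − s)/29 site-months: 2.69, 4.76, 6.21 and 7.03 for s = 3, 6, 9 and 12.
- Month 12 shared: the sum is 27.72, and SE = 2.5/√(27.72 × 2.64) = 0.29.
- Month 3 shared: the sum is 23.38, and SE = 0.32.

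**False positives with no true effect**, Φ(bias/SE − 1.96) + Φ(−bias/SE − 1.96):

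| Drift (g/kg/d per year) | Bias | Share of 1.9 | Two-sided false-positive rate |
|---|---|---|---|
| 0.1 | 0.15 | 8% | 7-8% |
| 0.25 | 0.36 | 19% | 21-24% |
| 0.5 | 0.73 | 38% | 63-70% |
| 1.3 | 1.90 | 100% | nearly 100% |

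**With calendar quarter added** (least squares on monthly site cells, all four choices of shared start), the bias from a common drift is 0.
- Sites 1-5 alone: SE 0.74-0.82, power for 1.9 about 64-72%.
- Sites 6-7 also informing the quarter effects: SE 0.45-0.48, power about 98-99%.

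Neither power figure allows for clustering, so both are optimistic.

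**Sensitivity of the multiplier.** The formula is (T + 3)/2/12 for T months of recruitment: 1.125 at T = 24 and 1.542 at T = 34. Placing the halt before the start point leaves it unchanged. Across wider layouts at 32 months (halt before or after the start point, all 552 infants or only about 383 at sites 1-5), false positives are 14-32% at a drift of 0.25 and 42-85% at 0.5.

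**The case against.** The strongest objection is that this is silence rather than error. The article is condensed, the analysis plan is not shown, the covariates are described as additional to a base model that is not fully listed, and the Discussion says time is considered. On that view, period terms belong in the analysis plan. This does not hold. Section {20a} does not stop at naming a mixed model. It lists what is forced in and omits the one confounder that the design creates. If calendar time sits in the unlisted selection pool, a p < 0.1 rule can discard it. The Discussion sentence names no term, and nothing in {20a} delivers what it describes.

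Several narrower objections do stand:

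- The drift rates are illustrative. At 0.1 per year the false-positive rate is only 7-8%.
- The 17.5-month gap depends on even accrual to month 32. Sections {16a} and {17a} aim for an equitable split of patients between groups. If each site's intervention phase only matched its control phase in length, the multiplier would be 0.95-1.07, and a drift of 0.5 per year would give 36-48% false positives.
- Calendar quarter removes only drift common to all sites. A drift of 1 g/kg/d per year at a single site would still leave a bias between about −0.68 and +0.54 with sites 1-5 alone.
- The Discussion's remark on growing parental involvement does not clearly mean an effect that builds with time since each site's start. It reads at least as naturally as a secular trend.
- Growth is one of several primary outcomes in {12}; training completion and kangaroo care are outside this point.

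**Conclusion.** The concern holds and needs correction. As written, the primary growth model cannot separate the intervention from secular change at sites 1-5. The bias is 1.46 times the annual drift under even accrual to month 32, and about 1 times the drift if phases are matched in length. Drift of either sign does harm: upward drift inflates the effect and downward drift masks it. The false-positive rates are conditional on assumed drift and on independent infants, and should be read as illustrations. The direction of the argument does not depend on them: with control always first and step order not randomised, a model with site and no calendar term is a before-after comparison. Section {20a} and the Discussion also disagree on whether time is in the analysis.

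**What to change.** In section {20a}, add calendar period (for example calendar quarter as a categorical fixed effect) to the terms forced into the primary growth model beside site and gestational age, and exempt it from backward selection. Make the time-adjusted contrast the primary result. State whether sites 6 and 7 contribute to the period effects, since this changes the standard error from 0.74-0.82 to 0.45-0.48. Add two sensitivity analyses: one in which the effect varies with months since the site's start, and one that allows time trends to differ between sites. Reword the Discussion sentence so that it describes the term actually fitted.

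The change is to wording and needs no new data. The cost is a wider interval: with sites 1-5 alone the standard error more than doubles. The calculation in {14} should be rechecked with period effects and clustering included. The choice should be fixed before outcome data are compared by group.
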